**Clinical evaluation lists**

- volume of intraoperative bleeding

- volume of postoperative bleeding

- postoperative clinical outcomes : MACE (MI, stroke, coma, arrest), renal failure, re-admission

Primary Outcomes

Increase (%) of GPIIb mRNA at 96 h postoperative time point (T6) compared to baseline (before initiation of surgery, T1)

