**Background**

There are some problems such as platelets aggregation, increase of platelets activation, and functional disorder leading to thrombosis formation or bleeding during intraoperative and postoperative periods in coronary artery bypass surgeries. Because arterial thrombosis formation can cause serious outcome, some studies investigated various factors to prevent platelet aggregation and to inhibit increase of coagulation of blood.

Previous studies suggested that abnormality of platelet function increased at postoperative period compared to preoperative period in cases which CPB was used in the operation. Therefore, there was a hypothesis that abnormality of platelet function caused by CPB would lesser develop in off-pump CABG compared to CABG. Bendar et al. presented that changes of platelet function by evaluating increase of p-selectin in patients who received OPCAB or CABG. They reported that increase of p-selectin as a platelet activation marker was highest at 2 days after operation in patients who received OPCAB. Lo et al. reported that platelet activation in terms of coagulation was maximized at immediate postoperative period in CABG, and between 20 – 96 hours after operation in OPCAB. There are some methodologies in evaluating platelet activation, that is, not only p-selectin but also flow cytometry by which antigen on the surface of platelet can be estimated. The most dominant platelet activation markers are p-selectin, PAC-1, CD 63. They can be used to evaluate blood disorders or responses to anticoagulants.

Aspirin was a most used anticoagulant in patients who received cardiac surgeries. It is well known that aspirin decrease platelet function and increase bleeding tendency in CPB. However, there has been any strong evidence supporting that aspirin administration lead to increase of postoperative bleeding.

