**Randomization**

All subjects will be randomly assigned with 1:1 ratio to two groups as following:

- Control group: patients receiving low dose aspirin (100 mg/day) until operating day
- Study group: patients stop aspirin (100 mg/day) 4 days before surgery

Random sequence will be made by a study nurse with size 2 blocks (AA, AB, BA, BB) including letter of ‘A’ (meaning aspirin continuation group) and ‘B’ (meaning aspirin discontinuation group). And then each generated letter will be concealed in an envelope in the order of generation. Enrolled patients will be allocated to their groups depending on the letter (A or B) inside the concealed envelopes that will be opened by an anesthesiologist who was unaware of the study.

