**Study protocol**

Assigned ward nurses will deliver drugs to all patients during the perioperative period.

In the aspirin continuation group (n=24), aspirin (100 mg; aspirin protect®, Bayer AG, Leverkusen, Germany) will be administered every morning until the operative day.

In the aspirin discontinuation group (n=24), aspirin will be stopped 4 days before the operative day.

Other anticoagulants, such as clopidogrel or warfarin will be stopped at least 5 days before surgery in all patients.

Anesthetic and surgical techniques will be standardized during the trial. A single anesthesiologist and a single surgeon, not aware of the group assignment, will perform OPCAB in all patients. All patients will arrive in the operating room without premedication. A catheter will be inserted at radial artery after local anesthesia for continuous arterial blood pressure monitoring. And standard monitoring including ECG, NIBP, SpO_2_ and BIS monitoring. Anesthesia will be induced with 0.15 mg/kg midazolam, 1-2 μg/kg sufentanil and vecuronium. After endotracheal intubation, mechanical ventilation will be applied to maintain an end-tidal carbon dioxide tension of 35-40 mmHg. Anesthesia will be provided with target-controlled infusion of propofol and remifentanil.

Target activated clotting time (ACT) will be 250-350 s.

1.5 mg/kg unfractionated heparin will be administrated before making of Y-graft.

At following time points, blood will be sampled for evaluation of platelet activation and responsibility.

- T1. Before skin incision
- T2. After reperfusion of graft
- T3. End of surgery
- T4. 24 h postoperatively
- T5. 48 h postoperatively
- T6. 72 h postoperatively
- T7. 96 h postoperatively

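### MACE is listed only as a postoperative outcome, so events between randomisation and surgery, when the arms differ by assignment, are not counted

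*Protocol*

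**What the plan says.** The protocol's Randomization section defines the arms by what happens before surgery: "Control group: patients receiving low dose aspirin (100 mg/day) until operating day" against "Study group: patients stop aspirin (100 mg/day) 4 days before surgery". The Study protocol section repeats this: "In the aspirin discontinuation group (n=24), aspirin will be stopped 4 days before the operative day". No postoperative difference in treatment between the arms is described.

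The Clinical evaluation lists contain three items. Two are bleeding volumes, one of them "volume of intraoperative bleeding" and the other its postoperative counterpart. The third is "postoperative clinical outcomes : MACE (MI, stroke, coma, arrest), renal failure, re-admission". No start or end time is given beyond the word *postoperative*, and no item covers the days before surgery.

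Statistical analyses states intention-to-treat. Criteria of drop-out lists intraoperative use of cardiopulmonary bypass, continuous haemofiltration or a balloon pump.

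**The concern.** The event window opens after the assigned treatment contrast has ended. A patient in the stop arm who has a stroke two days before the planned operation, while off aspirin by assignment, has no MACE event under the listed outcome. The same holds for a patient in the continuation arm, so the omission is symmetric in form. It is not symmetric in effect if stopping aspirin raises thrombotic risk in those days: the uncounted events would then fall mainly in the stop arm, and the MACE comparison would flatter stopping.

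The intention-to-treat statement does not repair this. It decides which patients are analysed, not which events count. Every randomised patient can be kept in the analysis and a preoperative infarction would still be scored as no event.

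The protocol says in its Background that there is no consensus on preoperative aspirin use. Readers are therefore likely to look at the clinical comparison even though it is secondary.

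**Working it through.** The point is mainly one of reading. The periods compare as follows.

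| Period | Arms differ by assignment? | MACE listed? | Bleeding listed? |
|---|---|---|---|
| Randomisation to surgery | Yes | No | No |
| During surgery | No new difference; earlier assignment carries over | Not clearly | Yes |
| After surgery | No new difference; earlier assignment carries over | Yes | Yes |

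*Preoperative period.* Assignment must be known by day -4 for the stop arm to be carried out, so at least 4 days of follow-up precede the event window. The first blood sample in the trial schedule is "T1. Before skin incision", when the assigned difference has already run its course. An event in those days could also delay or cancel the operation or make it emergent. Exclusion criteria name recent infarction, recent unstable angina, recent cerebral infarct, emergent operation and preoperative balloon pump. A patient with such an event after randomisation could thus come to match an exclusion criterion, and the protocol does not say that the event is still recorded.

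*Intraoperative period.* Bleeding is listed, MACE is not. Conversion to bypass or use of a balloon pump is a drop-out criterion and not an outcome.

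*Arm size.* Number of subjects gives 20 per group and a 20% loss rate: 20 x 1.20 = 24 per arm, 48 in total. This reproduces the protocol's figures.

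*Exposure outside the window.* 24 patients x 4 days = 96 patient-days off aspirin by assignment, if every patient has surgery on the planned day.

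*Weight of one event.* 1/24 = 0.042, or 4.2 percentage points of an arm.

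*Chance that the gap matters in practice.* The protocol gives no preoperative event risk, so a range of 0.5% to 5% per patient is assumed. The chance of at least one event among 24 patients is 1 - (1 - p)^24:

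- p = 0.5%: 11%
- p = 1%: 21%
- p = 2%: 38%
- p = 5%: 71%

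*What a complete count could show.* With no events among 24 patients, the one-sided 95% upper limit on the event rate is 1 - 0.05^(1/24) = 11.7%. A wider window would describe harm completely, but it would not give a powered comparison. It would not change the sample size of 48.

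**The case against.** The strongest reply is that this is a mechanistic trial. Purpose, hypothesis, sample-size rationale and primary outcome all concern platelet mRNA, and no safety or non-inferiority claim on MACE is made. The Background also places the platelet changes after surgery: activation highest at 2 days, or between 20 and 96 hours, after off-pump surgery, and gene expression at 3 to 6 days. On that reasoning a postoperative window looks where the authors expect the effect. This stands, and it limits the severity. It does not explain why an event during the assigned contrast should go uncounted.

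Four stronger readings are tempting, and the protocol does not support them.

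- *Harm from continuing aspirin is fully counted while harm from stopping is not.* Preoperative bleeding is unlisted too, so before surgery both sides of the trade-off are missing. The uneven capture of bleeding and MACE is confined to the operation itself.
- *The uncounted days are where stopping aspirin does most harm.* Nothing in the protocol says so. Its opening sentence speaks of platelet problems "leading to thrombosis formation or bleeding during intraoperative and postoperative periods in coronary artery bypass surgeries" and is silent on the preoperative days.
- *Nobody watches the patient during surgery, or before it.* Continuous arterial pressure is monitored, and the section adds "And standard monitoring including ECG, NIBP, SpO_2_ and BIS monitoring". An infarction or stroke that begins in theatre may be diagnosed and counted afterwards. The exclusion criteria also require preoperative laboratory tests. The accurate statement is that these periods are not covered by a listed event outcome.
- *The patients are in hospital from day -4, so collection costs nothing.* Ward nurses deliver drugs perioperatively, but admission by day -4 is not stated.

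A statistical analysis plan or safety procedure that is not shown may define events further. That lowers certainty that such events would go unrecorded. It does not remove the restriction that the protocol itself writes into the outcome.

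**Conclusion.** The concern holds as a point about the outcome window. The randomised difference is preoperative and the MACE outcome is postoperative, so a thrombotic event between randomisation and surgery counts in neither arm, and an arrest during surgery is not clearly counted. This is a stated window that is too narrow, not a detail left for later.

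The direction is conditional. If stopping aspirin causes preoperative thrombotic events, the MACE comparison leans towards showing that stopping is safe. If continuing aspirin causes preoperative bleeding, that is missed as well. The protocol gives no event risk, so the size of any bias cannot be stated; the 96 patient-days and the 4.2 points per event show exposure and granularity only. A reader might infer that the trial's conclusion is biased. It is not shown to be: the primary outcome is GPIIb mRNA and is untouched by this point. Severity is modest, because 24 per arm cannot compare rare events. The few events that occur should still all be described.

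**What to change.** In the Clinical evaluation lists, remove the restriction of MACE to the postoperative period. Count MACE and bleeding events from randomisation, or at the latest from day -4, to a stated postoperative day. Do this in every randomised patient, including those whose surgery is delayed, cancelled or becomes emergent and those who meet the drop-out criteria. Attribute each event to the assigned arm and report the counts descriptively in three periods: preoperative, intraoperative and postoperative. Re-admission stays postoperative by its nature.

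The cost is a change of protocol wording and a few case report form fields. If patients are not yet admitted on day -4, they also need to be asked about events at admission, and those whose surgery does not take place need a contact to obtain the same information. Sample size, treatment, sampling times and procedures do not change.

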**Statistical analyses**

Statistical analyses will be performed with intention-to-treat.

If data will be normal distributed, we will use student t-test or Chi square test. Otherwise, Mann-Whitney test or Fisher’s exact test will be used.

For the primary outcome, increase of GPIIb mRNA, independent t-test will be used.

For the evaluation discrepancy of platelet mRNA expression by aspirin effect between two groups at each time points, we will use the generalized estimating equation/general linear model. P-value < 0.05 will be considered to be significant.

Repeated-measures analysis and Bonferroni correction will be used for adequate analysis between groups.

Data will be presented as mean ± Standard deviation, median [interquartile range], and number of patients (%). All statistical analyses will be performed with IBM SPSS Statistics software (version 21, SPSS Inc., IBM Corporation, USA).

References

1. Bernard Lo, Rob Fijnheer, Domenico Castigliego, Cornelius Borst, Cor J. Kalkman, Arno P. Nierich, Activation of hemostasis after coronary artery bypass grafting with or without cardiopulmonary bypass. Anesth Analg 2004; 99: 634-40

2. Alessandro Parolari, Luciana Mussoni, Marta Frigerio, Moreno Naliato et al., The role of tissue factor and P-selectin in the procoagulant response that occurs in the first month after on-pump and off-pump coronary artery bypass grafting. The journal of thoracic and cardiovascular surgery 2005; 130(6): 1561-1566

3. Raymond Cartier, Current trends and technique in OPCAB surgery. J Card Surg 2003; 18: 32-46

4. Frantisek Bendar, Pavel Osmancik, Tomas Vanek, Heidi Mocikova, Martin Jares, Zbynek Straka, Petr Widmsky , Platelet activity and aspirin efficacy after off-pump compared with on-pump coronary artery bypass surgery: results from the prospective randomized trial PRAGUE 11-Coronary Artery Bypass and Reactivity of Thrombocytes (CABARET). The journal of thoracic and cardiovascular surgery 2008; 136(4): 1054-1060

5. Robert Poston, Junyan Gu, James Brown, James Gammie, Charles White, Jeffrey Manchio, Richard N. Pierson et al., Hypercoagulability affecting early vein graft patency dose not exist after off-pump coronary artery bypass. J of cardiothoracic and vascular anesthesia 2005; 19(1): 11-18

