There are various opinions on the perioperative use of aspirin for OPCAB or CABG. The Society of Thoracic Surgeons recommends stop of aspirin use 3 days before operation to minimize complications concerned with blood transfusion. American Society of Chest Physicians recommended continuous use of aspirin even at operation day. The American College of Cardiology and American Heart Association recommended stop of aspirin use 7-10 days before OPCAB or CABG. Jacob et al. reported that there was no difference between late discontinuation (stop 4 days before surgery) and early discontinuation (stop 7-10 days before surgery) on the perioperative complications.

Bednar et al. investigated the effect of aspirin administration at immediate postoperative periods on the level of Thromboxane B2 in patient who did not receive preoperative aspirin for CABG. The study reported that thromboxane B2 decreased significantly by postoperative aspirin administration. This study helped many physicians make a strategy of anticoagulants use in CABG.

Rally et al. presented that the model of most strong acute inflammation in human could be explained with coronary artery bypass surgery. They showed outbreak of expression of a gene influencing platelet at 3-6 days after surgery which could increase risk of myocardiac infarction. They evaluated 45 genes. GpIIb, GpIIIa, and Cox-1 gene expression did significantly increase by 3 times compared with baseline in all 11 subjects in the study. If any mRNA and protein which have a great role in platelet aggregation would increase due to CABG, this could be an important factor cause increase of thrombosis.

Because previous studies did not control preoperative use of anticoagulants, they could not reveal the effect of preoperative aspirin use on gene expression which influence platelet aggregation or platelet activation. There were numerous studies about co-effect of antiplatelet agents and anticoagulants on the activity of platelet. However, there has been no consensus about preoperative use of them. Therefore, strategies of perioperative use of them are various according to centers. Therefore, a study on the effect of preoperative low dose aspirin use on the mRNA which have a great role on platelet activation and platelet aggregation ant protein expression by it should be needed.

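### The protocol names a pooled-variance t-test without securing equal arms; naming Welch's t-test would be a cheap improvement

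*Protocol*

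**What the plan says.** Three parts of the protocol bear on this.

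- **General two-group comparisons** (Statistical analyses): "If data will be normal distributed, we will use student t-test or Chi square test". The alternative is "Otherwise, Mann-Whitney test or Fisher’s exact test will be used". The only stated condition for changing test is non-normality; unequal variance is not mentioned.
- **Primary outcome** (same section): "For the primary outcome, increase of GPIIb mRNA, independent t-test will be used". This does not say whether the pooled or the unequal-variance version is meant.
- **Arm sizes** (Randomization): "All subjects will be randomly assigned with 1:1 ratio to two groups as following", and the Study protocol section gives n=24 in each group. The list itself is described thus: "Random sequence will be made by a study nurse with size 2 blocks (AA, AB, BA, BB"). Number of subjects allows for 20% loss, and Criteria of drop-out removes patients for events that happen during surgery, after allocation.

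The same Statistical analyses section assigns mRNA by time point to a generalized estimating equation or general linear model, and between-group analysis to repeated measures with Bonferroni correction. It gives a significance rule ("P-value < 0.05 will be considered to be significant") and mentions no confidence interval. No SD is given for any outcome in either arm.

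**The concern.** Student's t-test estimates one SD from both arms together. Its standard error is right when the true SDs are equal, and nearly right when the arms are the same size. If both conditions fail, the error has a direction. When the smaller arm is the more variable, the standard error is too small and the test rejects too often. When the larger arm is the more variable, the standard error is too large and power is lost.

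The planned normality condition does not protect against this, because perfectly normal data can have unequal SDs. The protocol aims at equal arms, but its allocation list does not enforce them. At stake is the accuracy of P-values near 0.05 in a small trial, for the comparisons made by t-test.

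**Working it through.** **Inputs from the protocol.** 20 per group, 40 in total, 48 after allowing for 20% loss; 1:1 allocation; pairs AA, AB, BA, BB; significance at 0.05.

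**Assumptions.** Two-sided testing (sidedness is not stated); pairs drawn independently with probability 1/4 each; SD ratios of 1 to 3 (the protocol gives no SD).

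**Step 1. The plan's own figure.** 40 × 1.2 = 48, that is 24 per arm. (Dividing, 40/0.8 = 50; the two-patient difference does not matter here.) The base of 20 per arm cannot be reproduced, because no effect, SD or power is given.

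**Step 2. How unequal can the arms be?** A uniform draw from the four pairs is the same as two independent fair coin tosses, so one arm's size is Binomial(48, 0.5).

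- P(exactly 24/24) = 11%
- P(20/28 or worse) = 2 × P(X ≤ 20) = 31%
- Central 95% range: 17 to 31 per arm

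**Step 3. Why pooling misstates the standard error.** With arm sizes n1, n2 and SDs s1, s2:

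- true variance of the difference = s1²/n1 + s2²/n2
- average pooled estimate = [((n1−1)s1² + (n2−1)s2²)/(n1+n2−2)] × (1/n1 + 1/n2)

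Take s1 = 2 and s2 = 1.

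- n1 = 20, n2 = 28: true 4/20 + 1/28 = 0.2357; pooled (19×4 + 27)/46 × 0.0857 = 0.1919. The SE ratio is √(0.1919/0.2357) = 0.90, about 10% too small.
- n1 = 28, n2 = 20: true 4/28 + 1/20 = 0.1929; pooled (27×4 + 19)/46 × 0.0857 = 0.2366. The SE ratio is 1.11, about 11% too large.
- 24/24: both equal 5/24 = 0.2083. The SE is right on average.

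**Step 4. Rejection rates.** Simulation with normal data, equal means, nominal 5%, 200,000 runs per case; figures vary by about 0.1 point between runs.

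| Split and pattern | SD ratio 1.5 | 2 | 3 |
|---|---|---|---|
| 24/24, pooled | 4.9% | 5.1% | 5.4% |
| 20/28, larger SD in smaller arm, pooled | 6.7% | 7.9% | 9.2% |
| 20/28, larger SD in larger arm, pooled | 3.8% | 3.2% | 2.8% |
| 17/31, larger SD in smaller arm, pooled | 8.1% | 10.2% | 12.8% |
| 17/31, larger SD in larger arm, pooled | 3.0% | 2.1% | 1.5% |
| Welch, all of the above | about 5% | about 5% | about 5% |

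Averaged over all splits of 48 (20,000 runs per split), the pooled test rejects 5.4% at ratio 2 and 5.9% at ratio 3.

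**Step 5. Price of Welch if the SDs are in fact equal.** At a true difference of 0.91 SD, power is 86.92% pooled against 86.87% Welch at 24/24 (0.05 points) and 84.2% against 83.5% at 17/31 (0.7 points). At 16/24 and 0.9 SD it is 77.8% against 77.4% (0.4 points).

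**The case against.** The strongest reply is that nothing in the protocol shows unequal spread. This stands. No SDs are given, and the remark in Background that "The study reported that thromboxane B2 decreased significantly by postoperative aspirin administration" concerns the level of a marker in a cited study of aspirin given after surgery. It says nothing about spread, about stopping four days before surgery, or about GPIIb mRNA. A reader might infer that the protocol itself predicts unequal variances; it does not. The percentage scale of the primary outcome does not fill the gap either. Spread that grows with the mean gives unequal SDs only when the means differ, whereas the rates above assume equal means. If stopping aspirin changes nothing in the distribution, both arms share one SD and the pooled test is valid at any split.

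It can also be said that 1:1 with 24 per arm is the stated aim, that at 24/24 the error is trivial, and that averaged over splits it is under one point. This too stands, although the trial will have one realised split and not the average. Correcting the block list would remove most of the imbalance, leaving that from losses.

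Three further readings go too far. The primary analysis is not fixed as Student's test, since an independent t-test may be either version. The serial markers may fall under the repeated-measures analysis, so they cannot all be counted as t-tests. And no planned confidence interval is made wrong, because none is specified.

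What survives is that the protocol itself names Student's test in its general sentence, tied to normality alone, under an allocation list that does not hold the arms equal.

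**Conclusion.** The point holds as a cheap improvement and not as an error that invalidates the plan. A pooled test is named, unequal variance is not provided for, and equal arms are not secured. Under the assumed SD ratios of 1.5 to 3 at a 20/28 split, the true level of a nominal 5% test would be about 6.7 to 9.2% or 2.8 to 3.8%, depending on which arm is the more variable. Near-equal arms bring it back to about 5%. The 31% chance of such a split rests on independent, equally likely pairs; the SD ratios are assumptions with no figure in the protocol behind them. No change in sample size follows.

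**What to change.** In the protocol's Statistical analyses section, name Welch's unequal-variance t-test for the primary outcome and for the other two-group continuous comparisons that are made by t-test. Leave the outcomes analysed by generalized estimating equation, general linear model or repeated measures as they are. Do not make the choice depend on a preliminary test of equal variances.

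This takes one sentence and needs no new data or patients. If the SDs turn out equal, the price is under 0.1 points of power at 24/24 and about 0.4 to 0.7 points at the unequal splits examined.

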**Exclusion criteria**

Previous hematologic disease

Disorders of coagulation

Preoperative Plt. count < 100,000.

Preoperative PT INR > 1.2

Preoperative antithrombin III < 80% or 120%

Fibrinogen < 2g/L or 6g/L

Emergent operation

Reoperation of OPCAB

Combined operation with valvular surgery or aortic aneurysmal surgery

Hepatic disease

Renal disease

Recent MI within 12 months

Recent unstable angina within 10 days

Recent PCI history within 30 days

Implantation of Bare metal stent within 6 weeks

Implantation of drug eluting stent within 12 months

Recent cerebral infarct within 6 months

Heparin induced thrombocytopenia

Heparin resistance

Menstruation

No approval of study

Preoperative use of cardiopulmonary bypass, continuous veno-venous hemofiltration, or intraarotic balloon pump

Continuous use of other anticoagulants except aspirin such as plavix, heparin, low molecular weight heparin until operating day

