**Laboratory evaluation lists**

At the time points (T1, T2, T3, T4, T5, T6, T7)

- Platelet count

- Conventional coagulation tests (CCT : INR, aPTT, fibrinogen)

- Activated clotting time (ACT)

- Capillary closure time (PFA-100/EPI, PFA-100/ADP)

- D-dimer

- von Willebrand factor

- Rotational thromboelastometry (ROTEM)

- Platelet function (Verify/Now accumetrics)

- Platelet aggregation (multiplate , inducer : collagen, ADP, TRAP-6, arachidonic acid)

- Annexin V (flow cytometry)

- platelet P-selectin (flow cytometry)

- platelet CD41(flow cytometry)

- PAC-1 (flow cytometry)

- platelet CD63( flow cytometry)

- Thromboxan B2

At the time points (T1, T6)

- GPllb, GPllla, COX-1 mRNA (RT-PCR)

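### No covariate is named for the between-arm comparisons of platelet count and fibrinogen, although eligibility already requires a preoperative value of each; these non-primary comparisons are valid but less precise than they could be

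*Protocol*

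**What the plan says.** The Exclusion criteria section of the protocol turns patients away on "Preoperative Plt. count < 100,000", "Preoperative PT INR > 1.2" and "Fibrinogen < 2g/L or 6g/L", among other items. A patient cannot be declared eligible without these results.

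The Laboratory evaluation lists section then measures platelet count and "Conventional coagulation tests (CCT : INR, aPTT, fibrinogen") at every time point from T1 to T7. These are secondary laboratory outcomes; the primary outcome is the rise in GPIIb mRNA.

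The Statistical analyses section gives the general rule "If data will be normal distributed, we will use student t-test or Chi square test", with the Mann-Whitney or Fisher test otherwise. It adds an independent t-test for the primary outcome, a generalized estimating equation or general linear model for platelet mRNA, and a repeated-measures analysis with Bonferroni correction whose outcomes and terms are not listed. No covariate appears for any outcome.

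On timing, the Randomization section defines the contrast as "Study group: patients stop aspirin (100 mg/day) 4 days before surgery" against continuation until the day of operation. The Study protocol section defines the first blood sample as "T1. Before skin incision".

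**The concern.** A patient's own earlier value is the natural covariate for a later value of the same test. Here the earlier value has to be collected anyway, yet the named default is an unadjusted two-group test. With 20 evaluable patients per arm, variation between patients makes up a large part of the standard error, and a chance imbalance in the starting level of platelet count or fibrinogen passes straight into the arm comparison.

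The choice of baseline matters too. The obvious candidate in a T1 to T7 series is T1, but that sample is drawn at surgery, after one arm has stopped aspirin and the other has not. It is a post-randomisation measurement. For these tests the screening value avoids that problem.

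At stake is the width of the intervals for a few non-primary laboratory comparisons. The validity of the trial is not in question.

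**Working it through.** **Inputs.** The Number of subjects section gives 20 per group, 40 in total, raised to 48 for 20% loss. The 48 is reproduced as 40 × 1.2 = 48. The 40 cannot be re-derived, because no effect size, standard deviation or power is stated; it is used here as the evaluable number. The protocol gives no correlation between screening and later values, so a range is assumed.

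**Formula.** With N patients allocated 1:1 and p covariates explaining a share R² of the within-arm variance, the variance of the adjusted arm difference relative to the unadjusted one is

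(1 − R²) × (N − 3) / (N − 3 − p).

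The second factor is the price of estimating the covariate slopes. For N = 40 and p = 1 it is 37/36 = 1.028. The equivalent number of unadjusted patients is 40 divided by the ratio.

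| Assumed r | 1 − r² | Variance ratio | Standard error ratio | Equivalent patients |
|---|---|---|---|---|
| 0.1 | 0.99 | 1.017 | 1.009 | 39.3 |
| 0.2 | 0.96 | 0.987 | 0.993 | 40.5 |
| 0.3 | 0.91 | 0.935 | 0.967 | 42.8 |
| 0.5 | 0.75 | 0.771 | 0.878 | 51.9 |
| 0.7 | 0.51 | 0.524 | 0.724 | 76.3 |

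A simulation of 20,000 trials of 40 patients gave variance ratios of 1.016, 0.988, 0.771 and 0.512 at r = 0.1, 0.2, 0.5 and 0.7, in agreement.

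**Break-even.** The ratio equals 1 when r² = 1 − 36/37 = 0.027, that is r = 0.164. With three covariates together it is R² = 1 − 34/37 = 0.081, so one covariate per test is the better choice at this size.

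**If all 48 are evaluable.** The penalty is 45/44 = 1.023. The ratios are 0.767 at r = 0.5 and 0.522 at r = 0.7, equal to 62.6 and 92.0 patients instead of 48.

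**Does using T1 recover the gain?** Relative to the unadjusted variance, change from baseline has variance 2(1 − r). At the same correlation this exceeds 1 − r² by (1 − r)². At r = 0.5 it is 1.0, no gain at all; at r = 0.7 it is 0.6, against 0.524 for adjustment with the penalty included.

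**Bleeding volume.** With screening platelet count and fibrinogen as two covariates and an assumed multiple r of 0.2 (R² = 0.04), the ratio is 0.96 × 37/35 = 1.015 at N = 40 and 0.96 × 45/43 = 1.005 at N = 48: a slight loss. At an assumed 0.4 (R² = 0.16) it is 0.84 × 37/35 = 0.888 and 0.84 × 45/43 = 0.879.

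**The case against.** The strongest reply is that nothing in the Statistical analyses section is wrong here. Unadjusted comparisons are valid under randomisation, and covariates for secondary outcomes are commonly left to a statistical analysis plan, which is not shown. That stands as a limit on the weight of the point: it is a suggestion and not an error. It does not remove the point, because the protocol names an unadjusted test as its default and a better method is available from data it already requires.

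A second reply is that the repeated-measures analysis may be meant for these tests and already uses within-patient correlation. The text does not say which outcomes it covers. Even so, with complete data and equal correlation across time points, the arm contrast at a single time point gains nothing from modelling the other time points jointly, and subtracting T1 does worse than adjustment at the same correlation.

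Third, the sizes are hypothetical. This is fair. One correlation need not hold from before incision to 96 h after surgery, and none of these comparisons has a stated power. The timing of the screening tests is also inferred from their use for eligibility; the protocol gives no dates. As for T1, the background sections describe aspirin's effect on platelet function and thromboxane B2, not on platelet count or fibrinogen, so the reason to avoid T1 as baseline is its timing and not a demonstrated effect.

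A reader might infer more than the documents support:

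- That "volume of postoperative bleeding" should be adjusted for the same screening values. The documents give no correlation between bleeding and these tests, eligibility narrows their range, and at the lower assumed correlation precision falls.
- That the precision costs nothing. Each slope has to be estimated, and a weak covariate loses slightly at this size.
- That the screening tests are the only pre-randomisation data. Age, for one, is also known at entry.
- That the results would be biased or the primary outcome affected. Neither follows.

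**Conclusion.** The point holds as a minor matter of efficiency, limited to platelet count and fibrinogen, with INR optional because eligibility caps it at 1.2 and little gain is to be expected. At 40 evaluable patients the variance of the arm difference would fall by about 23% at r = 0.5 and 48% at r = 0.7, which makes standard errors about 12% and 28% smaller.

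This rests on three assumptions: that the screening values are taken before allocation, as their use for eligibility implies; that the relation is roughly linear; and that the correlation is at least moderate. Below about 0.16 the gain turns into a loss of under 3% in variance (at most 37/36 − 1 = 2.8%).

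**What to change.** Add to the Statistical analyses section that platelet count and fibrinogen at each time point are compared between arms with the patient's own screening value of that test as a covariate, and that INR may be treated the same way. State that T1 is not used as the pre-randomisation baseline, because it follows the start of the aspirin contrast, and is analysed as one of the follow-up time points. Leave bleeding volume and the primary outcome out of this change.

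The cost is one or two sentences and one degree of freedom per time-point model. If one model spans all time points and the screening slope is allowed to differ between them, one slope per time point is needed. No new measurement is required, but the screening values must be kept in the analysis data set and not only used to check eligibility.
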